### Recruitment

Participants will be identified either by physicians in expert centres, or by physicians in non-expert centres who then refer the patients to an expert centre. All eligible patients will be reviewed in a multidisciplinary team (MDT) meeting in an expert centre to assess whether the patient meets the inclusion and exclusion criteria. The multicentre, international involvement in this study will ensure adequate participant enrolment to reach the targeted sample size.

### Interventions

Eligible patients who have signed informed consent will be randomized by the coordinating investigator in a 1 : 1 ratio using a software randomization program (ALEA Clinical; FormsVision, Abcoude, the Netherlands). Patients will be stratified for previous chemotherapy, previous radiotherapy, and expert centre. After randomization, the treating surgical oncologist will refer the patient to the medical oncologist (experimental arm) or radiation oncologist (control arm).

The study flow chart is shown in *Fig. 1*, and study interventions and timelines for patients allocated to the experimental and control arms in *Tables 1* and *2* respectively.

**Fig. 1 zrab029-F1:**
[figure not shown]
Study flow chart B, blood samples for translational research; Q, questionnaires; CEA, carcinoembryonic antigen.

**Table 1 zrab029-T1:** Schedule interventions and assessments experimental arm

	Before allocation	After allocation			Follow-up	
	Outpatient clinic	Induction chemotherapy	Chemoradiotherapy	Surgery	Years 1–3	Years 4–5
**Screening**						
Eligibility screen	☒					
Informed consent	☒					
Randomization	☒					
**Interventions**						
Induction chemotherapy		☒				
Chemoradiotherapy			☒			
Surgery				☒		
Thoracoabdominal CT	☒	☒^*^	☒^†^		☒^¶^	☒^††^
Pelvic MRI	☒	☒^*^	☒^†^			
Questionnaires	☒				☒^#^	
CEA level					☒^**^	☒^¶^
Translational research: blood	☒	☒^*^	☒^‡^	☒^§^	☒^††^	
Translational research: tissue				☒		
**Assessments**						
Baseline characteristics	☒					
Toxicity of induction chemotherapy		☒				
Toxicity of chemoradiotherapy			☒			
Radiological response		☒	☒			
Pathological response				☒		
Surgical characteristics				☒		
Postoperative morbidity				☒		
Progression-free survival					☒^**^	☒^¶^
Local recurrence-free survival					☒^**^	☒^¶^
Disease-free survival					☒^**^	☒^¶^
Overall survival					☒^**^	☒^¶^
Quality of life	☒				☒^#^	
Costs	☒				☒^#^	

*After three (CAPOX) or four (FOLFOX/FOLFIRI) cycles;

† 4–6 weeks after finishing chemoradiotherapy;

‡ after finishing chemoradiotherapy and before surgery;

§ 3 months after surgery;

¶ 6-monthly;

# 3 and 12 months after surgery;

** 3-monthly;

†† yearly. CEA, carcinoembryonic antigen.

**Table 2 zrab029-T2:** Schedule interventions and assessments control arm

	Before allocation	After allocation		Follow-up	
	Outpatient clinic	Chemoradiotherapy	Surgery	Year 1–3	Year 4–5
**Screening**					
Eligibility screen	☒				
Informed consent	☒				
Randomization	☒				
**Interventions**					
Induction chemotherapy					
Chemoradiotherapy		☒			
Surgery			☒		
Thoracoabdominal CT	☒	☒^*^		☒^§^	☒^**^
Pelvic MRI	☒	☒^*^			
Questionnaires	☒			☒^¶^	
CEA level				☒^#^	☒^§^
Translational research: blood	☒	☒^†^	☒^‡^	☒^**^	
Translational research: tissue			☒		s
**Assessments**					
Baseline characteristics	☒				
Toxicity of chemoradiotherapy		☒			
Radiological response		☒			
Pathological response			☒		
Surgical characteristics			☒		
Postoperative morbidity			☒		
Progression-free survival				☒^#^	☒^§^
Local recurrence-free survival				☒^#^	☒^§^
Disease-free survival				☒^#^	☒^§^
Overall survival				☒^#^	☒^§^
Quality of life	☒			☒^¶^	
Costs	☒			☒^¶^	

* 4 to 6 weeks after finishing chemoradiotherapy;

† after finishing chemoradiotherapy and before surgery;

‡ 3 months after surgery;

§ 6-monthly;

¶ 3 and 12 months after surgery;

# 3-monthly;

** yearly. CEA, carcinoembryonic antigen.

#### Induction chemotherapy

Patients allocated to the experimental arm will start treatment with induction chemotherapy within 4 weeks after randomization. Induction chemotherapy will consist of either three 3-week cycles of CAPOX (oxaliplatin 130 mg per m^2^ body-surface area (BSA) intravenously (i.v.) on day 1, capecitabine 1000 mg per m^2^ BSA, orally, twice daily on days 1–14), four 2-week cycles of FOLFOX (85 mg per m^2^ BSA of oxaliplatin i.v. on day 1, 400 mg per m^2^ BSA of leucovorin i.v. on day 1, 400 mg per m^2^ BSA of bolus 5-fluorouracil i.v. on day 1 followed by 2400 mg per m^2^ BSA of continuous 5-fluorouracil i.v. on days 1–2), or four 2-week cycles of FOLFIRI (180 mg per m^2^ BSA of irinotecan i.v. on day 1, 400 mg per m^2^ BSA of leucovorin i.v. on day 1, 400 mg per m^2^ BSA of bolus 5-fluorouracil i.v. on day 1 followed by 2400 mg per m^2^ BSA of continuous 5-fluorouracil i.v. on days 1–2). The choice of chemotherapy agent will be left to the physician’s discretion.

After three cycles of CAPOX or four cycles of FOLFOX or FOLFIRI, pelvic MRI will be performed for local restaging, and high-dose thoracoabdominal CT for restaging of possible distant metastases. Restaging imaging will be discussed during a dedicated MDT meeting in one of the expert centres. If a patient develops distant metastases or local disease becomes unresectable, best palliative treatment will be offered according to the standard of care. If a patient has progressive local disease, but surgery is still considered feasible, no further systemic therapy will be administered and patients will start treatment with chemoradiotherapy. If a patient has stable or responsive disease, induction chemotherapy will be continued with either one 3-week cycle of CAPOX or two 2-week cycles of FOLFOX or FOLFIRI.

#### Chemoradiotherapy

Patients in the experimental arm will start chemoradiotherapy within 3–5 weeks after the first day of the last cycle of chemotherapy. Patients in the control arm will start chemoradiotherapy within 4 weeks after randomization. The radiotherapy dose will depend on whether the patient received radiotherapy previously. In radiotherapy-naive patients, full-course radiotherapy will consist of 25 × 2.0 Gy or 28 × 1.8 Gy radiotherapy. In patients with a history of radiotherapy, the radiotherapy dose will consist of 15 × 2.0 Gy. The target volume will be defined by the gross, clinical, and planning target volumes (GTV, CTV and PTV respectively), and will be similar for radiotherapy-naive and previously irradiated patients. The GTV contains all macroscopic visible tumour, the CTV includes the GTV with a margin of 1 cm, without adjustment of the CTV towards other organs, and the PTV includes the CTV with a margin that can be determined according to local policy. Concomitant chemotherapy will comprise capecitabine, administered orally at a dose of 825 mg/m^2^ twice daily on radiotherapy days. In the event of unacceptable toxicity caused by capecitabine during induction chemotherapy, concomitant tegafur/gimeracil/oteracil administered orally at a dose of 25 mg/m^2^ twice daily on radiotherapy days may be prescribed at the physician’s discretion.

#### Restaging

Four to 6 weeks after the last day of radiotherapy, pelvic MRI will be performed for local restaging and high-dose thoracoabdominal CT for restaging of possible distant metastases. Restaging imaging will be discussed during a dedicated MDT meeting in one of the expert centres. In the event of distant metastases or unresectable local disease, best palliative treatment will be offered. Patients with resectable disease will undergo surgery.

#### Surgery

Surgery will be performed by experienced surgical oncologists within 10–14 weeks after completion of chemoradiotherapy. The type of surgery will depend on the location of the recurrence and involvement of adjacent structures, and will be left to the discretion of the surgeon. When deemed necessary and feasible by the surgeon and radiation oncologist, intraoperative radiotherapy may be administered by either intraoperative electron beam radiotherapy or high-dose-rate intraoperative brachytherapy^38^^,^^39^.

#### Follow-up

Patients will be followed up at 3, 6, 9, 12, 15, 18, 21, 24, 27, 30, 33, 36, 42, 48, 54, and 60 months after surgery. At each follow-up point, a blood sample will be taken to determine the level of carcinoembryonic antigen (CEA). If the CEA level increases compared with the previous CEA level or the level rises above 5.0 µg/l during follow-up, high-dose thoracoabdominal CT will be performed. At 6, 12, 18, 24, 30, 36, 48, and 60 months after surgery, high-dose thoracoabdominal CT will be performed regardless of the CEA level.

#### Questionnaires

All participants will be asked to provide separate informed consent to receive validated quality of life questionnaires (European Organisation for Research and Treatment of Cancer QLQ-C30 and QLQ-CR29; EuroQol EQ-5D-5L™ (EuroQoL Group, Rotterdam, the Netherlands)). Patients will receive questionnaires at inclusion, and 3 and 12 months after surgery either by mail or digitally, according to their own preference.

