### Outcomes

The primary outcome of the study is the proportion of patients with a clear resection margin. A resection margin is considered clear (R0), if there are no tumour cells in any of the resection surfaces as determined by microscopy (resection margin more than 0 mm).

Secondary outcomes are:

3- and 5-year local re-recurrence-free survival, defined as the interval between surgery and local re-recurrence;3- and 5-year progression-free survival, defined as the interval between randomization and progression of local recurrence, local re-recurrence, distant metastases or death;3- and 5-year metastasis-free survival, defined as the interval between randomization and development of distant metastases;3- and 5-year disease-free survival, defined as the interval between surgery and local re-recurrence, distant metastases or death;3- and 5-year overall survival, defined as the interval between randomization and death;pathological response, graded according to the Mandard grading system^40^;radiological response, scored according to the magnetic resonance tumour regression grade (mrTRG);compliance rate with induction chemotherapy (i.e., the number of patients receiving CAPOX, FOLFOX or FOLFIRI as initial regimen will be tabulated, and dose modification and reason will be summarized for each regimen);toxicity of induction chemotherapy, scored from day 1 of the first cycle of induction chemotherapy until 1 month after the final administration, and graded according to the Common Terminology Criteria for Adverse Events (CTCAE) version 5.0;compliance rate with chemoradiotherapy, calculated as the total radiotherapy dose received divided by the total planned dose;toxicity of chemoradiotherapy, scored from start of radiotherapy until 3 months after the final dose of radiotherapy, and graded according to CTCAE version 5.0;number of patients undergoing surgery;surgical characteristics (e.g., type of resection, ostomy, use of intraoperative radiotherapy, blood loss, duration of operation, intraoperative complications);major surgical morbidity rate scored from the date of surgery to 3 months after surgery, and graded according to the Clavien–Dindo classification^41^;quality of life, assessed with EQ-5D-5L™, QLQ-C30 and QLQ-CR29 questionnaires at inclusion, and at 3 and 12 months after surgery; andcost-effectiveness and cost–utility, based on Dutch costing guidelines for healthcare, the case report forms, and the EQ-5D-5L™ questionnaire.

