### Statistical methods

Demographics, patient, and tumour characteristics will be presented for each treatment arm. Continuous data will be reported as mean (standard deviation) or median (interquartile range or 95 per cent confidence interval), depending on the distribution. Categorical data will be reported as count with percentage. All statistical tests will be two-sided and *P* < 0.050 will be classified as statistically significant. Patients initially randomized but considered ineligible afterwards, based on information that should have been available before randomization, will be excluded from all analyses.

Analysis of the primary endpoint of this study, the proportion of patients with an R0 resection, will be based on the intention-to-treat principle using Fisher’s exact test. In addition, a per-protocol analysis will be performed as a sensitivity analysis.

All survival curves will be constructed according to the Kaplan–Meier method, and the log rank test will be used to compare treatment arms, adjusting for stratification factors at randomisation (previous radiotherapy, previous systemic therapy, and expert centre). In addition, hazard ratios will be calculated using a Cox proportional hazards regression model, adjusting for stratification factors. Metastasis-free survival, progression-free survival, and overall survival will be based on the intention-to-treat group. Local re-recurrence free survival and disease-free survival analyses will include only patients who underwent surgery.

Data on surgical characteristics, histopathological characteristics, and major surgical morbidity will be presented by treatment arm, and will be derived only for patients who underwent surgery. The number of patients undergoing surgery will be analysed in the intention-to-treat population. Comparison between treatment arms will be done by means of Fisher’s exact test.

The absolute and relative incidence of toxicities related to the administration of induction chemotherapy or chemoradiotherapy will be presented by treatment arm, and analysed in all patients who received at least one dose of neoadjuvant chemotherapy (experimental arm) or chemoradiotherapy (control arm). Comparison between treatment arms will be done by means of Fisher’s exact test.

Comparison of health-related quality of life between the two treatment arms at baseline and over time will be performed by means of a random-effects regression model and will be based on the intention-to-treat group.

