Incremental cost-effectiveness and cost–utility ratios will be calculated for the extra costs per additional surviving patient and the extra costs per additional quality-adjusted life year respectively. Non-parametric bootstrapping, drawing samples of the same size as the original samples and with replacement, will be applied to generate 95 per cent confidence intervals for (differences in) costs and health outcomes. Cost-effectiveness planes will be displayed and cost-effectiveness acceptability curves drawn for willingness-to-pay values up to €100 000.

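### Every post-baseline quality-of-life and EQ-5D-5L questionnaire is timed from surgery, so the intention-to-treat comparison has no scheduled follow-up data for patients not operated and none during neoadjuvant treatment

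*Protocol article*

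**What the plan says.** The Questionnaires section of the protocol article states: "Patients will receive questionnaires at inclusion, and 3 and 12 months after surgery either by mail or digitally". The Outcomes section gives the same timing: "quality of life, assessed with EQ-5D-5L™, QLQ-C30 and QLQ-CR29 questionnaires at inclusion, and at 3 and 12 months after surgery". Tables 1 and 2 agree. The Questionnaires, Quality of life and Costs rows are marked before allocation and in follow-up years 1–3, with the footnote "3 and 12 months after surgery". They have no mark under induction chemotherapy, chemoradiotherapy or surgery.

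Statistical methods says of the arms: "Comparison of health-related quality of life between the two treatment arms at baseline and over time will be performed", and that this "will be performed by means of a random-effects regression model and will be based on the intention-to-treat group". The cost–utility ratio is "the extra costs per additional quality-adjusted life year", and Outcomes names EQ-5D-5L as one of its data sources.

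The Sample size section expects a quarter of patients not to reach surgery because of progression or death from it. Under Induction chemotherapy and Restaging, patients with metastases or unresectable disease leave the curative pathway for palliative care. The Follow-up section also counts its visits from the operation, ending at "42, 48, 54, and 60 months after surgery". No other time origin is given for patients who are not operated.

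**The concern.** The stated analysis population and the data collection do not fit together. An intention-to-treat comparison over time needs outcome data on everyone randomised. Here every measurement after baseline depends on surgery, which happens after randomisation and which treatment may affect. The Introduction itself says that induction toxicity could hinder later treatment and that a longer neoadjuvant course may raise the risk of unresectability. The trial hypothesis points the other way, to better local control.

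Three things are at stake:

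- Patients who progress before surgery have no scheduled questionnaire after inclusion.
- The period in which the arms differ most, induction chemotherapy, has no quality-of-life or utility measurement, although toxicity and loss of performance status are among the drawbacks that the Introduction lists.
- The same nominal visit falls at different times from randomisation in the two arms, so the arms are not compared at a common time.

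A statistical analysis plan cannot repair this, because the data would not exist.

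**Working it through.** **1. The plan's own figures.** R0 among those starting treatment: 0.75 × 0.60 = 0.45, as stated. Sample size for 45% versus 60%, two-sided 5%, 80% power, no continuity correction: 173 per arm (power 80.05%). Allowing for 5% dropout: 346 / 0.95 = 364.2, against 364 stated. These reproduce, so 25% and 364 can be taken as the protocol's planning values.

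**2. Patients with no scheduled post-baseline questionnaire.**
- 25% in both arms: 0.25 × 364 = 91, about 45 per arm (0.25 × 346 = 86.5 without the dropout allowance).
- At most 364 − 91 = 273 (75%) can then contribute follow-up data, before deaths, non-response and refusal of the separate questionnaire consent.
- The share not operated in the experimental arm is not stated. A 60% intention-to-treat R0 rate equals share operated × R0 rate among those operated. If the latter is 60%, 80% or 100%, the share operated is 100%, 75% or 60%. So 0% to 40% are not operated.
- With 182 per arm and 25% in the control arm (45.5 patients), the total runs from 45.5 + 0 = 45.5 to 45.5 + 0.40 × 182 = 118.3, or about 46 to 118.

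**3. Timing from randomisation.** Week of surgery = s + d + r + g, where:
- s = 0–4 weeks to first treatment (both arms start within 4 weeks);
- d = time from first chemotherapy to chemoradiotherapy, which is 0 in the control arm;
- r = 3 to 5.6 weeks of radiotherapy (15 or 28 fractions; five per week assumed);
- g = 10–14 weeks to surgery.

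For full induction without delays, the fourth CAPOX cycle starts at week 3 × 3 = 9 and the sixth FOLFOX/FOLFIRI cycle at week 5 × 2 = 10. Adding the 3–5 weeks in the Chemoradiotherapy section gives d = 12–14 or 13–15 weeks.

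| | Surgery (week) | First post-baseline questionnaire (+13 weeks) |
|---|---|---|
| Control | 0+0+3+10 = 13 to 4+0+5.6+14 = 23.6 | 26 to 36.6 |
| Experimental, full CAPOX | 0+12+3+10 = 25 to 4+14+5.6+14 = 37.6 | 38 to 50.6 |
| Experimental, full FOLFOX/FOLFIRI | 0+13+3+10 = 26 to 4+15+5.6+14 = 38.6 | 39 to 51.6 |

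For patients alike in s, r and g, the difference between arms is d, that is 12 to 15 weeks. With full induction the two windows for the first questionnaire do not overlap. If induction stops at restaging for local progression, the last cycle starts at week 6 under either schedule and d is 9–11 weeks.

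**4. Consequence for the model.** A random-effects model uses every available record, but an unoperated patient supplies only a baseline value. The model then in effect gives that patient the course of operated patients with a similar baseline. This is valid only if progression to unresectability carries no further information about later quality of life, which is hard to defend. For QALYs, utilities from inclusion to at least week 26 (control) or week 38 (experimental), and all later utilities of unoperated patients, rest on no scheduled measurement.

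**The case against.** The best defence is that timing from surgery has a purpose: it compares the arms at the same stage of recovery. Visits fixed from randomisation would catch them at different stages. That stands, and is why the post-surgery questionnaires should stay. It answers a question about operated patients, however, not the intention-to-treat question that the article sets. It is also fair that these are secondary outcomes under separate consent, and that 25% is a planning figure.

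A reader might infer more than the documents support:

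- **That the bias favours induction.** If induction brings more patients to surgery, the control arm loses more of its patients with poor prognosis, and the bias goes against induction. If induction leads to more unresectability, it goes the other way. The experimental-arm share is not stated, so the direction is unknown.
- **That all clinical assessment starts at surgery.** Restaging MRI and CT, and toxicity recording, take place before it in both arms.
- **That surgery-based visits distort progression-free survival.** Tables 1 and 2 schedule its assessment every three months in years 1–3, so a shift of 12–15 weeks is about one visit interval. Patients not operated because of progression have already had their event.
- **That cost–utility is declared intention-to-treat, or that costs are missing.** No population is named for it, and resource use can also come from case report forms.
- **That QALYs will be interpolated in a particular way, or that the baseline comparison is an error.** The article gives no interpolation rule, and the form of baseline adjustment belongs to the analysis plan.

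**Conclusion.** The point holds for quality of life and utilities. The questionnaire schedule is stated in two sections and both tables, without conflict, so it is not a detail lost when the protocol was condensed. Followed as written, about 91 of 364 patients would have no scheduled post-baseline questionnaire, assuming 25% not operated in each arm. The figure is about 46 to 118 if only the control share is fixed at 25% and the experimental R0 rate is 60%. No utility is measured during neoadjuvant treatment in either arm. The 12- to 15-week misalignment assumes full induction, no delays and otherwise equal intervals.

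The planned comparison is thus labelled intention-to-treat but is in effect one among operated patients. Its bias cannot be signed from the documents. The schedule should be changed while data can still be collected. The primary endpoint and the sample size are unaffected.

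**What to change.** Keep the questionnaires at 3 and 12 months after surgery for the comparison at equal recovery. Add the same EQ-5D-5L, QLQ-C30 and QLQ-CR29 forms for all consenting randomised patients, operated or not, at times counted from randomisation and identical in both arms. At least one should fall in the neoadjuvant phase. Name these as the data for the intention-to-treat quality-of-life comparison and for the QALY calculation, and update the Questionnaires and Outcomes sections and Tables 1 and 2 accordingly.

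At the same times, record vital status and metastasis status for patients not operated. Overall and metastasis-free survival run from randomisation by intention to treat, and the article gives these patients no follow-up schedule.

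The cost is a small amendment, a few more mailed or digital forms per patient, and some added patient burden and data handling. Treatment, the primary analysis and the number of patients do not change.
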